#### Validity

The validity of active monitoring items will be assessed against relevant clinical assessments (ie, PANSS and CDSS) using Spearman correlation. An exploratory analysis will also be conducted to understand the association between mobility indicators, corresponding contextual questions in active monitoring, and PANSS negative symptom scores. We define a moderate statistically significant correlation (ie, Spearman rho>0.35) as the validity threshold.

#### Feasibility Parameters

To assess the feasibility of the study, we collected detailed recruitment and retention data accordant with the CONSORT statement for feasibility studies [41], including (1) number of eligible participants consenting; (2) completeness of outcome measures; (3) number of participants lost to follow-up; and (4) reason for withdrawal. We defined Green (>80%; ie, feasible and no changes needed), Amber (60%-80%; ie, additional elements required to increase feasibility), and Red (<60%; ie, not feasible) categories to indicate the levels of feasibility for the above parameters. We will explore app usage and engagement data guided by the Analyzing and Measuring Usage and Engagement Data framework [63].

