## Results

Recruitment for the study was initiated in August 2022. Of the 47 participants who were approached for the study from August 2022 to October 2022, 41 participants agreed to take part in the study. Reasons for not participating included concerns that answering app questions would be a burden (n=1) and family member concerns that answering app questions might be triggering for the participant (n=1). Another 4 participants declined to participate without giving any reason. We excluded 1 participant for not meeting the inclusion criteria, leaving a total of 40 participants taking part in the study. As of December 2022, 40 participants had completed the study. We expect to report the validity of the app-based monitoring and results for feasibility on the (1) number of eligible participants consenting, (2) completeness of outcome measures, (3) number of participants lost to follow-up, and (4) reasons for withdrawal. We also expect to report participants’ overall impressions of YouXin, positive and negative aspects of the app in terms of content and usability, perceived helpfulness of the app, barriers and facilitators to engagement, and views on the training session.

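### The feasibility bands run in the wrong direction for loss to follow-up and cannot be applied to reasons for withdrawal: a modest wording error in a stated decision rule

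*Protocol article*

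**What the plan says.** The Feasibility Parameters section of the protocol article names four parameters. The first two are "1) number of eligible participants consenting; (2) completeness of outcome measures". The text then runs from the other two straight into the top band of the scale: "3) number of participants lost to follow-up; and (4) reason for withdrawal. We defined Green (>80%; ie, feasible and no changes needed".

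The middle band is "Amber (60%-80%; ie, additional elements required to increase feasibility", and the bottom band, which also fixes the scope of the rule, is "Red (<60%; ie, not feasible) categories to indicate the levels of feasibility for the above parameters". The section gives no reversal, complement or exemption for any of the four.

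The Results section lists the same four parameters as findings still to be reported, again as loss rather than retention. On completion it says: "As of December 2022, 40 participants had completed the study". The Statistical Analysis Plan section says only that recruitment and retention data will be summarised descriptively. Nothing elsewhere in the article adjusts the rule.

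**The concern.** A single rising scale works only if every parameter improves as its percentage rises. Consent and completeness do. Loss to follow-up worsens as it rises, so the wording gives the best rating to the heaviest attrition and the worst rating to none. The fourth parameter is a different problem: a reason is a category, so there is nothing to compare with 60% or 80%.

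Feasibility is one of the stated aims, and the Abstract and Discussion make integrating the app into clinical workflows depend on it. The bands are the only rule in the article that converts data into a feasible or not-feasible label. Study Design also makes the monthly recruitment target of 10 a feasibility outcome, but attaches no such labels to it. A traffic-light rule is useful because it can be applied mechanically. Two of the four inputs to this one do not allow that.

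**Working it through.** **Inputs.** Enrolled: n = 40 (Study Design; Recruitment; Results). Bands: Green above 80%, Amber 60%-80%, Red below 60% (Feasibility Parameters). Completed: 40 (Abstract; Results). Approached 47, agreed 41, excluded as ineligible 1 (Results). The article states no classification of its own, so there is no published figure to reproduce. The recruitment counts are consistent: 47 − 1 − 1 − 4 = 41, and 41 − 1 = 40.

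**Cut-offs as counts.** 60% of 40 = 24 and 80% of 40 = 32. A count of 0-23 is therefore Red, 24-32 Amber and 33-40 Green.

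**Parameter 3 as worded.** Percentage = 100 × lost / 40. **As retention.** Percentage = 100 × (40 − lost) / 40.

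| Number lost | % lost | Band as worded | % retained | Band as retention |
|---|---|---|---|---|
| 0-7 | 0-17.5 | Red | 82.5-100 | Green |
| 8-16 | 20-40 | Red | 60-80 | Amber |
| 17-23 | 42.5-57.5 | Red | 42.5-57.5 | Red |
| 24-32 | 60-80 | Amber | 20-40 | Red |
| 33-40 | 82.5-100 | Green | 0-17.5 | Red |

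The two readings agree only for 17-23 lost, which is 7 of the 41 possible counts (0 to 40). For 0-7 and 33-40 lost they are exact opposites.

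**Applied to the reported result.** If completing the study means completing follow-up, then 40 − 40 = 0 lost. As worded: 100 × 0/40 = 0%, Red. As retention: 100 × 40/40 = 100%, Green.

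**Parameter 1, for comparison.** 41/47 = 87.2%. With the ineligible person removed from both counts, 40/46 = 87.0%. Both are Green, so the scale runs the right way for consent.

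**Parameter 4.** No percentage is defined, so no band can be assigned. This is separate from the direction error and plays no part in the Red result above.

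**The case against.** The strongest reply is that the intention is plain. Feasibility Parameters introduces the list as recruitment and retention data, and the Statistical Analysis Plan section uses the same description. The bands also carry meanings, and nobody would call the loss of more than four fifths of a sample feasible with no changes needed. The only workable reading is percent retained, and on that reading 40 of 40 is as far from every cut-off as it can be. This stands, and it limits the point to a wording error. It does not make the written rule correct, because the text still bands the number lost and the Results section repeats that form.

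A reader might infer more: that the study has failed its own feasibility rule, or that the authors are free to choose a favourable reading now that completion is known. The documents support neither. No sensible competing reading exists to choose between, and 100% retention leaves no room for choice. The zero-loss figure is itself an inference, since the article gives no loss count and lists that number among results still to come.

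It can also be said that reasons for withdrawal appear in the list simply as data collected, so the lack of a band removes no real verdict. That is fair as to consequence, but the sentence setting the bands still covers all four items.

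Finally, exact numerators and denominators are detail that an article may leave to the full protocol. Their absence is not part of this point.

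**Conclusion.** The point holds as a modest error in a stated decision rule, of minor to moderate weight. As worded, the rule misclassifies loss to follow-up for every count except 17-23 of 40, and it cannot classify reasons for withdrawal at all. The reported completion would be labelled Red as worded and Green as retention. That comparison assumes that the 40 who completed the study all completed follow-up, and that the denominator is the 40 enrolled. Because retention was probably what the authors meant, the published conclusion on feasibility is unlikely to change.

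**What to change.** Restate the third parameter as the percentage of enrolled participants retained at the 4-week assessment and apply the existing cut-offs to it unchanged. With 40 enrolled, 0-7 lost is Green, 8-16 Amber and 17-40 Red. Take reasons for withdrawal out of the banded parameters and report them descriptively. Make the same change where the Results section repeats the list. Since completion has already been reported, present this openly as a clarification of wording that leaves the cut-offs as published. The cost is about a sentence of text, with no new data and no new analysis.

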#### Acceptability

The quantitative feedback questionnaire (QFQ) was given to participants at the 4-week timepoint to collect quantitative information regarding acceptability. The QFQ is a 27-item questionnaire designed to assess the acceptability of utilizing smartphone app interventions for service users. It has been used in previous digital mental health studies for people with psychosis [64,65].

Qualitative interviews were conducted to explore their experiences using Youxin including (1) overall impressions of YouXin, (2) positive and negative aspects of the app in terms of content and usability, (3) how it helped or did not help, (4) what changes they would make, (5) barriers and facilitators to engagement, and (6) views on the training session.

#### Safety

To evaluate the safety of the app, detailed adverse events and serious adverse events were collected and reported using standardized operating procedures in line with National Institute for Health and Care Research and Health Research Authority Safety Reporting procedures.

### Safety Considerations, Adverse Events, and Risks

We did not expect participating in the study would cause any significant risks. Although the study involves people with severe mental health problems, the eligibility criteria for the study require the participants to be stable and at low risk for self-harm or harm to others, as judged by a clinician. There is the potential for participants to report elevated levels of distress because of taking part in assessments and digital self-monitoring. This may include the potential for increasing awareness of one's own symptoms. Participants were informed during the recruitment process that they may encounter such situations, and they were encouraged to discuss this with the research team if they feel distressed during the study.

### Statistical Analysis Plan

All quantitative analyses will be performed using R (version 4.0.5) [66]. Feasibility data and safety data including (1) recruitment and retention data, (2) app usage data, (3) completeness of study measures, and (4) the number and nature of adverse events will be analyzed using appropriate descriptive statistics (mean and standard deviations for continuous data; counts and percentages for categorical data). Logistic regression and linear regression analyses will be used to explore sociodemographic and clinical characteristics and device attributes as predictors of feasibility (eg, dropouts, app usage).

The active monitoring will generate 3 levels of data, with the data entered for each “beep” as level 1, nested within the level 2 “day” level, which is nested within the level 3 subject level. Because the PANSS and CDSS measure participants’ symptoms for the past week, and to minimize the impact of missing data, the subject level mean score of the first week will be used to calculate the association between active monitoring items score and relevant symptom domain scores of the PANSS and CDSS at the week 1 follow-up assessment to evaluate validity. The significance level for the study will be set to .05. Cronbach alpha will be used to calculate the internal consistency reliability of the sets of the items of active monitoring. To account for the nested structure of the data, multilevel models will be used to explore the instability of the different constructs across time and patterns of missing data.

The GPS mobility indicators will be extracted from passive monitoring data. The convergent validity of passive monitoring will be calculated by the correlation between GPS mobility indicators and the PANSS negative symptom score. Discriminant validity of passive monitoring will be demonstrated by low correlation between GPS mobility indicators and positive symptoms measured by PANSS.

Qualitative data will be transcribed verbatim in Chinese and then translated to English by the principal researcher. A framework analysis approach will be used based on the protocol by Braun and Clarke [67], which consists of the following 6 phases of thematic analysis: familiarization, transcription, generating initial codes, searching for themes, reviewing themes, and defining and deciding on meaningful themes. Nvivo software (version 12) [68] will be used to manage the qualitative data.

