Third, recall bias has long been identified as a limitation of conventional clinical assessment methods [11,14]. Service users, especially people with severe mental health problems for which cognitive impairments are common [15], may have trouble accurately recalling their thoughts, feelings, and behaviors over a preceding period of time, making recall experiences at a granular level challenging [16]. Therefore, to optimize the quality of assessment and capture symptom fluctuation in a real-time, real-world granular manner, more ecologically valid assessment methods are needed.

The aforementioned barriers affect countries worldwide [14], even high-income countries with sophisticated mental health service systems (eg, the United Kingdom and the United States) [17,18], and China has been no exception to these challenges.

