### Study Design

The study uses a mixed methods design consisting of a nonrandomized feasibility study and a nested qualitative acceptability study. The study was designed according to the Consolidated Standards of Reporting Trials (CONSORT) statement extension for pilot and feasibility studies [41]. We recruited 40 people with psychosis at a tertiary-level psychiatric hospital in Beijing, China. This number is in line with other feasibility studies and sufficient to report on response rates, follow-up rates, safety information, and attrition, as well as the clinical characteristics of our study population at the beginning of the study and at follow-up [42]. Formal power calculations for treatment effects are not appropriate for a study primarily aimed at establishing feasibility. This sample size means a monthly recruitment target of 10 participants. Moreover, monitoring the recruitment target is part of the feasibility outcomes.

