**Figure 2 figure2:**
[figure not shown]
The coproduction process.

The phases of the coproduction process.Alpha:The alpha phase aims to understand the end users’ (clinicians and service users) needs for using digital tools to monitor symptoms and demonstrate the preliminary design with users (the ClinTouch app and the user interface prototypes of the YouXin app). The design, contents, and functions of the app were further developed based on the feedback from users.Beta:The principal researcher and software engineer integrated the feedback and delivered a functional prototype that users could install on their phones. During the meeting, users tested the app and provided feedback.Live:A fully developed digital platform was presented to users (3 clinicians and 3 people with psychosis) to try out for a week. This meeting focused on evaluating the usability and acceptability of the app and any major issues regarding implementation.

YouXin has 2 core functions: active monitoring of symptoms (ie, smartphone survey) and passive monitoring of behavioral activity (ie, passive data collection via embedded smartphone sensors). The app is available for both Android and iOS platforms. The active monitoring uses a time-contingent design. To minimize participant assessment burden and increase compliance, in accordance with a previous similar study [38], prompts were set to alert at 2 pseudorandomized timepoints per day, during a 12-hour interval from 10 AM to 10 PM, 7 days a week for 4 weeks. A minimum 1-hour increment was set between each prompt on a particular day to avoid clustering of responses. Participants could either snooze (5 minutes or 30 minutes) or decline answering the prompt. Based on previous works by the research group, on average, it takes 70 seconds to complete each prompt. Smartphone sensors passively collected GPS data every 5 minutes. According to a recent systematic review [39], passive sensing was feasible for measuring negative symptoms; specifically, GPS indicators were associated with apathy, avolition, asociality, and anhedonia [48,49]. All collected data were uploaded to a secure server at Beijing Anding Hospital.

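### Reliability of the app's item sets rests on ordinary Cronbach alpha at an unstated level, so no within-person reliability is planned although instability over time will be analysed

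*Protocol article*

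**What the plan says.** All the relevant analysis statements are in one paragraph of the Statistical Analysis Plan section of the protocol article.

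- Structure: "The active monitoring will generate 3 levels of data", with each prompt at level 1, inside a day, "which is nested within the level 3 subject level".
- Validity: "the subject level mean score of the first week will be used to calculate the association between active monitoring items score and relevant symptom domain". The clinical side is PANSS and CDSS at week 1, so the unit here is the participant mean.
- Reliability: "Cronbach alpha will be used to calculate the internal consistency reliability of the sets of the items of active monitoring". No level and no multilevel version is given.
- Nesting: in the sentence that follows, "multilevel models will be used to explore the instability of the different constructs across time and patterns of missing data". Reliability is not in that list.

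Under Study Intervention and Procedures, "prompts were set to alert at 2 pseudorandomized timepoints per day", every day for 4 weeks. Study Design gives 40 participants. The Background argues that symptoms can fluctuate daily and that better methods are needed to "capture symptom fluctuation in a real-time, real-world granular manner".

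**The concern.** Internal consistency has a different meaning at each level of these data. Between people, it asks whether participants who score high on one item over the study also score high on the others. Within a person, it asks whether the items rise and fall together from one occasion to the next. An item set can do well on the first and badly on the second.

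The plan will analyse instability over time, which is a within-person quantity, and the Background gives capturing fluctuation as a reason for this kind of measurement. If an item set has low within-person reliability, much of the apparent instability may be item-specific variation or error rather than change in the symptom. The one coefficient named would not show this at either level where it might plausibly be computed. The article also says that app-based versions of these measures have not been validated in Chinese among people with psychosis, so within-person reliability cannot be taken for granted.

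**Working it through.** The article states no reliability figure, target or item count, so there is nothing of its own to reproduce. The check asks what an ordinary alpha would show if the two levels differ.

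**Inputs from the article.** 40 participants; 2 prompts a day over 4 weeks. That is 2 × 7 = 14 prompts in week 1, 2 × 7 × 4 = 56 per person, and 40 × 56 = 2,240 in all at full response.

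**Assumed inputs.** k = 5 items; ICC = 0.6 (share of item variance lying between people); inter-item correlation 0.6 between people and 0.1 within people.

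**Formulas.** Standardized alpha = k·r / (1 + (k − 1)·r). For pooled prompts, r = ICC × r_between + (1 − ICC) × r_within. For week-1 participant means, the within-person part is divided by 14, taking prompts within a person as independent.

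**Base case.**
1. Between-person: 5 × 0.6 / (1 + 4 × 0.6) = 3.0 / 3.4 = 0.88.
2. Within-person: 5 × 0.1 / (1 + 4 × 0.1) = 0.5 / 1.4 = 0.36.
3. Pooled prompts: r = 0.6 × 0.6 + 0.4 × 0.1 = 0.40; alpha = 2.0 / 2.6 = 0.77.
4. Week-1 means: within part 0.4 / 14 = 0.0286; r = (0.6 × 0.6 + 0.0286 × 0.1) / 0.6286 = 0.577; alpha = 2.886 / 3.309 = 0.87.

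So either single-level version could look acceptable (0.77 or 0.87) while the within-person figure is 0.36.

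**Range.** With k = 5 and between-person r = 0.6, varying ICC over 0.5–0.7 and within-person r over 0.05–0.2:
- lowest pooled: r = 0.5 × 0.6 + 0.5 × 0.05 = 0.325; alpha = 1.625 / 2.3 = 0.71; within-person 0.25 / 1.2 = 0.21;
- highest pooled: r = 0.7 × 0.6 + 0.3 × 0.2 = 0.48; alpha = 2.4 / 2.92 = 0.82; within-person 1.0 / 1.8 = 0.56.

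**Where the gap closes.** With ICC 0.6 and within-person r = 0.4, pooled r = 0.36 + 0.16 = 0.52, pooled alpha = 2.6 / 3.08 = 0.84 and within-person alpha = 2.0 / 2.6 = 0.77. With both correlations at 0.6, every version is 0.88.

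**Where pooled alpha gives no false comfort.** With k = 3, ICC 0.3, between-person r = 0.5 and within-person r 0.05–0.10, pooled alpha is only 0.41–0.46.

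**Simulation.** 500 data sets of 40 persons × 28 days × 2 prompts, k = 5, between-person r = 0.8, 30% of within-person variance at day level, full response. Mean alphas:

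| ICC | Within-person r | Pooled | Week-1 means | Within-person |
|---|---|---|---|---|
| 0.5 | 0.05 | 0.78 | 0.93 | 0.21 |
| 0.7 | 0.05 | 0.86 | 0.94 | 0.21 |
| 0.6 | 0.10 | 0.84 | 0.94 | 0.36 |

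The mechanism therefore holds at this design's size.

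**The case against.** A reader might infer that alpha will be run on the pooled prompts and will therefore mix the two sources of variance. The article does not say so. It names no level, and the only scoring unit it fixes in that paragraph is the participant mean for the validity analysis. If alpha uses that unit, the mixing criticism largely falls away and the coefficient suits the correlation it accompanies. This part of the objection stands.

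It can also be said that the level of a supporting coefficient is the kind of detail an article leaves to a fuller plan. That is fair for the level alone. But the article does choose a coefficient, and it lists what the multilevel models are for without including reliability. The mismatch with the planned instability analysis is in the text as written.

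A reader might also infer that the validity result is undermined, or that alpha will in fact mislead. Neither follows. The validity criterion (Spearman rho above 0.35) and the traffic-light feasibility categories do not use alpha, and nothing in the article says alpha will support a claim about change within a patient. The illustration assumes low within-person correlations, so it shows what could happen, not what will.

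Finally, multilevel factor models with 40 people at the upper level may be imprecise or fail to converge. That bears on the choice of remedy and is reflected there.

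**Conclusion.** The point holds in a limited form. The plan recognises three-level data and will analyse instability over time, yet the only reliability coefficient it names is ordinary alpha at an unstated level. At neither plausible level does that coefficient show whether the item sets reliably track change within a person.

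The possible size is a pooled alpha of 0.77 against a within-person alpha of 0.36 in the base case, and 0.71–0.82 against 0.21–0.56 over the range shown. These figures rest wholly on assumed item numbers and correlations, with within-person correlations set low. The gap narrows as those correlations rise and is zero when the two levels agree.

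This is a modest improvement to a supporting analysis in a feasibility study. No stated conclusion on validity or feasibility turns on it.

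**What to change.** For each item set, report between-person and within-person reliability separately, with confidence intervals. As the main method, use generalizability coefficients from a variance decomposition by person, day and prompt, with items as a facet. Report multilevel omega only if the model converges with 40 participants. An ordinary alpha may stay as a descriptive figure if its level is stated.

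Tie each coefficient to its use: the between-person one alongside the week-1 correlation with PANSS and CDSS, and the within-person one for any statement about instability or fluctuation.

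The cost is a little more analysis in R on data already collected. The downsides are imprecise between-person estimates with 40 participants and possibly a less favourable reliability figure.

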Participants were given a training session by the principal researcher to help them navigate the app after they consented to take part. During the training, the principal researcher helped the participant download the app onto their smartphone and gave a demonstration of the app. Participants had the opportunity to practice using the app and ask questions during the process; they had access to the app from the training session until the 4-week timepoint. An opt-out approach was applied to give participants autonomy to switch on or off the passive sensing section during the study.

The principal researcher provided technical support as needed during the study; no clinical care was provided by the research team (clinical care continued as usual from the service). The participant was referred to their treating clinician for appropriate mental health care should any clinical issues be raised to the research team. Participants were informed at the training sessions that the app is not suitable for seeking urgent medical care while in any emergency circumstance.

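### A low sample correlation with PANSS positive symptoms in at most 40 people is too imprecise to demonstrate discriminant validity of the GPS indicators, and it is not compared with the convergent correlation

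*Protocol article*

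**What the plan says.** The Statistical Analysis Plan section sets two separate checks for passive monitoring. Convergent validity is the correlation of the GPS mobility indicators with the PANSS negative symptom score. For the other check it says: "Discriminant validity of passive monitoring will be demonstrated by low correlation between GPS mobility indicators and positive symptoms measured by PANSS". It gives no value for *low* and does not set the two correlations against each other.

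The only numerical rule for a correlation is in the Validity section: "We define a moderate statistically significant correlation (ie, Spearman rho>0.35) as the validity threshold". The significance level is also fixed: "The significance level for the study will be set to .05".

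On sample size, Study Design says "We recruited 40 people with psychosis at a tertiary-level psychiatric hospital in Beijing, China" and Results says "As of December 2022, 40 participants had completed the study". Study Intervention and Procedures adds: "An opt-out approach was applied to give participants autonomy to switch on or off the passive sensing section during the study". The number with usable GPS data is therefore at most 40 and is not stated. Passive Monitoring names three indicators: home time, distance travelled and location clusters.

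**The concern.** Discriminant validity is a claim about the true correlation: the GPS indicators should follow negative symptoms and should not follow positive symptoms to the same degree. A low value in a sample of 40 or fewer says little about that, because the interval around it is wide.

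The substantive claim is also comparative. If an indicator simply tracks overall severity, its true correlations with the two scales are equal. Two noisy estimates of the same value can still fall on opposite sides of two separate cut-offs. Following the stated rule, GPS could then be reported as specific to negative symptoms when it is not. Validity is one of the study's named aims, so the wording of this conclusion matters even in a feasibility study.

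**Working it through.** The article gives no precision or power figure for these correlations, so there is no figure of its own to reproduce.

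**Inputs**
- n = 40 (Study Design, Results). 30 and 20 GPS users are assumed as illustrations of opt-out.
- Alpha 0.05 (Statistical Analysis Plan), taken as two-sided because sidedness is not stated.
- Threshold rho>0.35 and significant (Validity). It is assumed to apply to the convergent GPS check.
- *Low* is undefined. |rho|<0.30 and |rho|<0.20 are assumed.

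**Step 1: precision of a low rho.** Use the Fisher z transform with the Spearman standard error SE = sqrt((1 + r²/2)/(n - 3)), and limits tanh(atanh(r) ± 1.96 SE).

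For r = 0.10 and n = 40: SE = sqrt(1.005/37) = 0.165 and atanh(0.10) = 0.100. The z limits are 0.100 ± 0.323, that is -0.223 and 0.423. Back-transformed, the interval is -0.22 to 0.40.

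| Observed rho | n = 40 | n = 30 (assumed) | n = 20 (assumed) |
|---|---|---|---|
| 0 | -0.31 to 0.31 | -0.36 to 0.36 | -0.44 to 0.44 |
| 0.10 | -0.22 to 0.40 | -0.27 to 0.45 | -0.36 to 0.52 |
| 0.20 | -0.12 to 0.48 | -0.18 to 0.53 | -0.27 to 0.59 |

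For the upper 95% limit to lie below 0.35 at n = 40, the z value must be below atanh(0.35) - 1.96 × 0.1645 = 0.365 - 0.322 = 0.043, so the observed rho must be about 0.04 or less.

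**Step 2: two separate checks when nothing discriminates.** Simulate trivariate normal data (20,000 samples per setting) in which the indicator correlates 0.35 with both PANSS scales and the scales correlate 0.2 or 0.4 with each other (assumed). The indicator is oriented so that the hypothesised association is positive. A false pass is a convergent rho above 0.35 and significant, together with a low positive-symptom rho.

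| Meaning of low (assumed) | False pass per indicator, n = 40 | n = 30 | n = 20 |
|---|---|---|---|
| abs(rho) < 0.30 | 14-17% | 13-17% | 9-12% |
| abs(rho) < 0.20 | 5-7% | 6-8% | 5-6% |

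These runs set the underlying Pearson correlation to 0.35, which is a Spearman rho of about 0.336. A check with the true Spearman rho itself at 0.35 gave 13-16% and 5-7% at n = 40, so the scale makes little difference. With three indicators the chance of at least one false pass is larger, but the indicators will be correlated, so no joint figure is given.

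**Step 3: what the direct comparison can deliver.** In the same simulations the SD of the difference between the two rhos at n = 40 is 0.17-0.19. An approximate 95% interval is therefore ± 1.96 × 0.17 = ± 0.33 to ± 1.96 × 0.19 = ± 0.37.

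**The case against.** A low correlation with an unrelated construct is the usual form of a discriminant criterion. A reader might infer that the plan treats a non-significant result, or a failure to find a correlation, as proof that none exists. The text does not support this: it says low, and significance appears only in the threshold for claiming validity. Error rates based on non-significance are therefore not used here. For the same reason one cannot say that a smaller GPS sample makes the claim easier to reach. Under a fixed cut-off the false-pass rate does not rise materially as n falls, and with |rho|<0.30 it declines by n = 20.

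A reader might also infer that excluding clinically unstable people narrows the positive-symptom scores and favours a low rho. That direction is not established. Eligibility was deliberately broad, covering the schizophrenia spectrum and clinical high risk, which may widen the spread.

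Nor is there a clear contradiction with the Validity section. The sentence beginning "An exploratory analysis will also be conducted to understand the association between mobility indicators" goes on to name contextual questions and negative symptom scores, and does not mention positive symptoms.

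Finally, a cut-off, intervals and a test for dependent correlations could sit in a fuller plan, and their absence alone would be no finding. Study Design also says "Formal power calculations for treatment effects are not appropriate for a study primarily aimed at establishing feasibility", and the Green, Amber and Red rules do not use GPS validity. All of this limits the severity. What remains is that the published sentence commits to a conclusion that a low sample rho in at most 40 people cannot support.

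**Conclusion.** The point holds as a minor one. A low observed rho in 40 or fewer people does not demonstrate discriminant validity: at n = 40 even an observed 0.10 is compatible with true values from about -0.22 to 0.40, beyond the article's own 0.35. Judging the two correlations separately also allows an indicator that tracks both scales equally to be called specific, in about 14-17% of studies per indicator (low as |rho|<0.30) or 5-7% (low as |rho|<0.20).

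The percentages rest on assumed cut-offs, normal data, a true correlation of 0.35 with both scales and an inter-scale correlation of 0.2 to 0.4. The interval in Step 1 needs none of these cut-offs or correlations, but assumes that all 40 gave GPS data; it widens with fewer. The severity is minor because this is a secondary GPS analysis in a feasibility study and no progression rule depends on it.

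**What to change.** For each GPS indicator:
- Report its Spearman correlations with PANSS negative and PANSS positive scores, each with a 95% confidence interval and the number of participants contributing GPS data.
- Estimate the difference between the two correlations in the hypothesised direction, with a participant-level bootstrap 95% interval or a test for dependent correlations.
- Claim discriminant validity only if that interval excludes 0 in the hypothesised direction. Otherwise report it as not shown.

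Replace *demonstrated* with *explored* in the Statistical Analysis Plan section.

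The cost is a change of wording and a short bootstrap on data already collected. The downside is that, with an interval of roughly ± 0.33 to ± 0.37 around the difference at n = 40, the likely answer is inconclusive.
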